## Materials and methods

### Objectives and endpoints

The overall goal of this protocol is to evaluate our intensive 12-week community-based exoskeleton training program. The International Classification of Functioning, Disability, and Health (ICF) provides a comprehensive framework for description and assessment of functional abilities split across four domains: body structures and functions, activities and participation, personal, and environmental factors [39, 40]. The ultimate goal of an intervention study is to improve activity and participation. Given this is analogous to a phase I study, our endpoints here aim to evaluate changes at the ICF level of function and activity, with the goal to provide an initial body of evidence to support more comprehensive studies of this and similar technologies in the future.

The primary objective is to evaluate the safety and effectiveness of a longitudinal community exoskeleton training program to improve crouch gait in children with CP or knee extension deficiency in children with MD, SB, or iSCI. To evaluate this objective, the primary endpoint is change in peak knee angle during midstance phase of walking (without the exoskeleton) between two time points: the initial and final outcome assessments. These assessments occur immediately before and after the 12-week community-based exoskeleton training period. A clinically significant improvement in peak knee extension will be considered here as greater than 10°, based on a study characterizing children with crouch gait as mild, moderate or severe in terms of 10° increments [41]. This change in peak knee extension will also be compared to the change measured between the assessments immediately before and after the 12-week standard therapy period as a secondary endpoint. This outcome is at the ICF level of body structure and function.

The secondary objectives at the ICF level of body structure and function are as follows.

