### Hypotheses

We hypothesize that regular use of a robotic exoskeleton in the community setting will lead to functional improvement in overground walking without the exoskeleton by (i) increasing peak knee extension angle, (ii) improving overground gait speed, and (iii) improving knee extensor (vastus lateralis and rectus femoris) muscle activation and strength. We hypothesize that these improvements will be greater than changes measured before and after the 12-week standard therapy period. We further hypothesize that community-based exoskeleton training will increase motor function and mobility, which will be assessed using clinically validated scales of activity and mobility. Finally, we hypothesize that observed functional improvements as a result of the 12-week community intervention training period will persist following completion of the training, as measured during the follow-up assessment.

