### Statistical considerations

Sample size was determined from pilot data collected during a prior, in-lab protocol performed at NIH Clinical Center (#13-CC-0210) using the same exoskeleton. We used the targeted mean improvement in peak knee extension during midstance, which was approximated as 10.0 degrees, with an observed standard deviation of ± 3 degrees (n = 3) and a safety factor of 4 given the previously observed variability in response to our exoskeleton [26], resulting in a computed effect size of 0.86. At a significance level of 0.05 and 90% power we estimate that 13 participants within each subject pool is required based on power analysis for a paired t-test. We estimated about 80% of enrolled participants would complete the study through the final outcome assessment, and additionally considered 25% would complete the protocol, but elect out of the community use portion. In order to ensure 13 participants have completed the required study components, we determined at most 22 participants would need to be recruited for each subject pool, setting the maximum number of participants as 44.

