Our continuous data outcomes will be summarized using descriptive statistics and presented as means with standard deviation. We will summarize our categorical data as a range with percentages. The primary endpoint, peak knee angle at midstance, will be analyzed using a per-protocol analysis to include all participants who completed at least 80% (9 weeks) of the study intervention in the community using a paired t-test between the initial and final outcome assessments. Similarly, a paired t-test will be utilized to compare change in the primary endpoint of peak knee extension with the change observed over the 12-week standard therapy block. Given the potential for carryover effects, this secondary outcome will only be assessed using data from the first intervention period from each group. We will test for normality and if not found, we will use the signed rank test instead of the paired t-test. Given the potential heterogeneity within each participant pool, we anticipate the possibility for a wide range of responses in the endpoints following the intervention. To address this potential variability, we will also perform a post-hoc linear regression analysis to assess potential effects of age, weight/height, and mobility (characterized by functional scale GMFCS I-IV) on each endpoint. We will perform an interim analysis of the primary endpoint when we have reached 50% of the estimated recruitment number to evaluate the effect and the power and revise the total enrollment number if indicated.

The same statistical procedures will be used for the secondary outcome measures and exploratory outcome measures that evaluate continuous data between multiple time points. We will report the 95% confidence intervals, in addition to the mean difference and statistical significance of that difference, for each endpoint. For the exploratory analysis of dosage effect across all four outcome assessments, we will use a repeated measures ANOVA.

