There are several potential limitations to the current study. First, the study intervention takes place outside the clinical environment. While this approach enables the participants to tap the potential for wearable robotic exoskeletons in providing high dosage of intensive gait therapy, it also requires the participant (and their parent/caretaker) to administer the intervention. We previously completed an initial study comprised of 10 visits using the NIH-Agilik exoskeleton in the clinical setting including treadmill and overground walking and observed increased participant comfort and familiarity with the exoskeleton across the visits [36]. Further, our lab previously performed a home-based clinical trial of elliptical training in this same target population and age range that required training 5 days/week for 12 weeks [52]. We therefore believe the proposed home-based exoskeleton intervention is feasible. Yet, it is possible that compliance in completing the prescribed dosage (1 hr/day, 5 days/week) will be variable. To mitigate this, we will track usage during weekly check-ins and provide positive reinforcement in completing the required training. Post-hoc, our analysis will include adherence to the prescribed dosage as a correlate if necessary to account for variable usage. Second, participant growth during the study could be pose multiple challenges, including to the fit of the exoskeleton device as well as changes in gait biomechanics. To mitigate the former, we will include height adjustment in the custom exoskeleton that will enable lengthening the ankle-to-knee distance by up to 3 inches. Our randomized design also includes a 12-week standard therapy period, which will be utilized to control for growth and development between subjects, but it is possible that growth-linked changes in biomechanics will still be present between the intervention and standard therapy periods which will be controlled for as a covariate in the analysis if necessary. Further, our study design does not include a washout period between the exoskeleton and standard therapy interventions. In theory, a washout period allows participants to return to baseline after treatment, but our target population are children who experience natural growth and development and regularly receive physical therapy to maintain and improve daily functioning, which we chose not to ask participants to stop as would be necessary to ensure washout. As a result, carryover effects are possible and we will limit our comparison between the two interventions to the first intervention period for each group. Finally, there is the potential for technical challenges because intervention delivery requires successful operation of the robotic exoskeleton. While we are confident that the exoskeleton and its associated electronics, actuators and sensors are sufficiently robust for use outside the clinical environment, it is possible that unanticipated technical issues may arise that require interrupting the intervention period to perform repairs or adjust the device and control settings, which may affect protocol adherence.

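### The powered primary test of effectiveness is an uncontrolled before-after comparison, and the controlled comparison behind the superiority hypothesis has no stated power and is not powered at the planning SD

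*Protocol article*

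**What the plan says.** In the protocol article, *Objectives and endpoints* opens: "The primary objective is to evaluate the safety and effectiveness of a longitudinal community exoskeleton training program". The primary endpoint is the change in peak knee angle at midstance between the initial and final assessments, which bracket the 12-week community exoskeleton block. Comparison with the change over the standard-therapy block is named there as a secondary endpoint.

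*Statistical considerations* fixes the primary analysis as per-protocol, "using a paired t-test between the initial and final outcome assessments". The sample size sets a target gain of 10 degrees and takes its spread from pilot data: "observed standard deviation of ± 3 degrees (n = 3) and a safety factor of 4". For 90% power at alpha 0.05, the section concludes: "13 participants within each subject pool is required based on power analysis for a paired t-test". Because carryover is possible, the comparison with standard therapy uses only each group's first period. *Study population* says that the two diagnostic pools are analysed separately.

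Other sections ask more of the controlled comparison. *Hypotheses* says: "We hypothesize that these improvements will be greater than changes measured before and after the 12-week standard therapy period". The *Discussion* presents the comparison with the standard-therapy block as the way efficacy will be determined, and adds: "Our randomized design also includes a 12-week standard therapy period, which will be utilized to control for growth and development between subjects". No sample size or power is given for it.

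**The concern.** The test that carries the power and the primary label uses neither the randomisation nor the standard-therapy period. The participants are aged 3 to 17, are growing, and are not asked to stop physical therapy. Their 12-week change mixes any device effect with development, usual therapy, familiarity with the tests and regression to the mean. A significant result would show that knee extension changed, not that the exoskeleton changed it.

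The comparison that could support a causal claim is secondary, uses one period per child and is made within each pool. A reader who sees 90% power beside a superiority hypothesis may take a non-significant controlled result as evidence of no difference, when the data could not have settled the question.

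**Working it through.** **1. The plan's own figure.** Inputs from *Statistical considerations*: improvement 10 degrees, SD 3 × 4 = 12 degrees, stated effect size 0.86 (10/12 gives 0.833), alpha 0.05, n = 13 per pool. For a paired t-test the noncentrality is d√n = 0.86 × √13 = 3.10 on 12 df.
- One-sided (critical t 1.782): power 89.9%.
- Two-sided (critical t 2.179): power 81.2%.

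The stated 90% at 13 is therefore matched by a before-after test at a one-sided level. Recruitment also reproduces: 13 / (0.80 × 0.75) = 21.7, rounded up to 22 per pool. The effect in this calculation is an improvement from zero; no control quantity enters.

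**2. What the before-after test also detects.** Suppose, purely as an illustration, that 5 degrees of change would occur without the device. With SD 12 and n = 13 the noncentrality is (5/12) × √13 = 1.50. The paired test is then significant in 28% of trials two-sided and 41% one-sided, with no device effect at all.

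**3. Power of the controlled comparison.** Restricting it to first-period data means that different children are compared, so a two-sample t-test applies, with noncentrality (10/SD) / √(1/nA + 1/nB) on nA + nB − 2 df. Assumptions not in the document: 1:1 allocation, two-sided 0.05, the same SD of change in both groups, and a 10-degree between-group difference (that is, no change on standard therapy, which favours the trial). The SDs of 9 and 6 are assumed values that show sensitivity to the planning SD. Example: 7 v 6 with SD 12 gives 0.833 / 0.556 = 1.50 on 11 df.

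| Contributing children per pool | SD (degrees) | Power for 10 degrees |
|---|---|---|
| 7 v 6 | 12 | 28% |
| 7 v 9 | 12 | 34% |
| 7 v 11 | 12 | 37% |
| 11 v 11 | 12 | 46% |
| 7 v 6 | 9 | 45% |
| 7 v 6 | 6 | 78% |

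Using the stated 0.86 instead of 0.833 gives 29% at 7 v 6 and 48% at 11 v 11.

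**4. Precision.** The 95% CI half-width at 7 v 6 with SD 12 is 2.201 × 12 × √(1/7 + 1/6) = 14.7 degrees. That is wider than the 10 degrees the article treats as clinically significant. With SD 6 it is 7.3 degrees.

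**5. Size for 90% power.** At SD 12 the comparison needs 32 children per group in each pool (30 at d = 0.86), or 64 (60) per pool, against a maximum of 22 recruited.

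**6. If children on standard therapy also improve.** A between-group difference of 5 to 7.5 degrees (assumed) at 7 v 6 with SD 12 has power of 11% to 18%.

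**The case against.** The strongest defence is that this is a disclosed choice in an early-phase trial. The article calls the study analogous to phase I or I/II, says that it seeks initial efficacy to support larger trials, and openly labels the controlled comparison secondary. A within-participant primary test is defensible at that stage. This justifies the small size. It does not make uncontrolled change evidence of effectiveness.

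Several stronger readings are tempting, and the documents do not support them:
- *The trial ignores its randomised control.* It does not. The comparison is planned for the primary measure and for the secondary endpoints. The control is absent only from the primary, powered test.
- *The article claims 90% power for superiority.* It attaches that figure to a paired t-test and nothing else. The gap is that nothing is said about power for the comparison that the hypothesis needs.
- *The Discussion contradicts the analysis on growth.* It does not say that the primary t-test controls for growth. The controlled comparison, with growth as a covariate if necessary, can serve that purpose.
- *The controlled comparison has 28% power.* That is one point in a range. The SD of 12 is a pilot SD from three children, deliberately multiplied by four. The 7 v 6 split assumes that only the 13 exoskeleton completers contribute, whereas a Group B child's first period is standard therapy and could count without completed exoskeleton training; the article does not say.
- *The true power of the primary test is about 80%.* That presumes a two-sided test. Sidedness is not stated, and this is a separate matter.

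The article also promises a 95% CI and mean difference for each endpoint, which already reduces the risk of misreading a non-significant result.

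**Conclusion.** The concern stands as a mismatch between claim and test. Effectiveness is a primary objective, but its powered analysis has no control. Superiority over standard therapy is hypothesised, but it rests on a secondary between-group comparison with no stated power. At the planning SD of 12 degrees that comparison has roughly 28% to 46% power per pool for a 10-degree difference, depending on how many children contribute. Only a considerably smaller SD brings it near conventional levels (78% at 7 v 6 with SD 6). These figures assume 1:1 allocation, a two-sided 0.05 test, equal SDs and no change on standard therapy; a smaller true difference lowers them. The planned interim analysis, which may revise enrolment, looks only at the primary endpoint and so does not address this comparison.

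**What to change.** 1. In the objectives and analysis text, describe the Initial-Final paired test as within-participant change over the exoskeleton block. Base any conclusion of effectiveness, or of superiority over standard therapy, on the first-period randomised contrast within each pool. Report it as a between-group difference with 95% CI, adjusted for the pre-randomisation Baseline value. Group A's Initial value should not be the covariate, because it is measured after exoskeleton accommodation and so may already reflect treatment. For the same reason, state which visits define the change in each group.
2. In *Statistical considerations*, say that the stated power applies only to the within-participant paired test. Add that the controlled contrast is not powered at the planning SD, giving the range and its assumptions. Say that it will be read as an estimate, so that non-significance is not taken as no difference.

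The cost is a change of wording and one specified analysis; no extra participants are needed. The downside is a more modest claim from the primary result.

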**Fig 2 pone.0304087.g002:**
[figure not shown]
Schematic diagram of the randomized, cross-over protocol. Yellow indicates the 12-week block for exoskeleton set-up and in-lab accommodation. Pink indicates the 12-week block for community exoskeleton use, including a 6-week follow up period. Blue indicates the 12-week block for standard therapy in the community.

The design is structured as a randomized crossover study with two intervention arms: (i) exoskeleton intervention and (ii) standard therapy control (Fig 2). The crossover design was chosen to maximize participation by allowing all participants to receive the exoskeleton intervention. After enrollment, each participant will be randomized into one of two groups: Group A will receive the exoskeleton intervention first, followed by standard therapy control, while Group B will complete standard therapy control first before crossing over to receive the exoskeleton intervention. Continuation of the participant’s existing standard therapy was chosen as the control due to limited resources to administer a common program and because individuals in the target populations are often enrolled in a physical therapy regimen. All participants will complete an initial visit for exoskeleton fitting, setup, and calibration as well as multiple in-lab accommodation visits prior to starting the community-based exoskeleton intervention. An alternative option, if the participant is not able to complete the community use portion of the protocol for any reason, is to continue the intervention by completing a lab-based exoskeleton training consisting of 10 total visits, each with a target of 1-hour total of walking with the exoskeleton. The target intervention dosage in the community will be held constant across all subjects who participate at 1 hour/day, 5 days/week. Outcomes from individuals who complete the lab-based training will be analyzed separately from those who complete the community-based intervention. The maximum possible number of visits to NIH for completion of this study is 19. All visits will take no more than 4 hours to complete. There will be up to six outcome assessments to evaluate our primary, secondary and exploratory objectives.

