## Discussion

This randomized, cross-over study was designed to evaluate the safety, feasibility, and effectiveness of a gait training intervention delivered outside the clinical environment using a wearable robotic exoskeleton. The cross-over design was chosen to enable each participant to receive the experimental intervention, thereby maximizing the incentive for participation while also allowing each to serve as their own control. Additionally, while there is an emerging body of evidence suggesting that exoskeleton-mediated gait training can be effective, at least in the short term, at improving gait biomechanics and self-selected walking speed [14, 15, 31], these initial studies have all been performed in the clinical setting. This study will address the current gap in the scientific literature regarding the use of these mobile technologies outside that environment, despite their unique design for this precise application. Indeed, wearable exoskeletons are a powerful potential tool for delivering the intensive therapy dosages that are required for successful re-training of movements such as stepping and walking [37, 38], and this study is intended to provide a starting point for future deployment of these technologies.

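### The comparison with standard therapy is given a paired test but limited to first-period data, in which no child supplies a pair

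*Protocol article*

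**What the plan says.** All references are to the protocol article.

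- **Test.** Statistical considerations first describes the paired t-test for the primary endpoint (Initial to Final assessment, within child). For the contrast with standard therapy it continues: "a paired t-test will be utilized to compare change in the primary endpoint of peak knee extension with the change observed". The comparator is the block of 12 weeks on standard therapy.
- **Data.** The next sentence reads: "Given the potential for carryover effects, this secondary outcome will only be assessed using data from the first intervention period from each group". The limitations paragraph of the Discussion repeats this: "we will limit our comparison between the two interventions to the first intervention period for each group".
- **Fallback.** If normality is not found, "we will use the signed rank test instead of the paired t-test".
- **Order of treatment.** Study design, in the text below Fig 2: "Group A will receive the exoskeleton intervention first, followed by standard therapy control, while Group B will complete standard therapy control first".
- **Reach.** "The same statistical procedures will be used for the secondary outcome measures and exploratory outcome measures" that are continuous and measured at several time points. Objectives and endpoints says that changes in the secondary endpoints will also be compared with changes over the standard therapy period.
- **Sample size.** Statistical considerations derives 13 participants per pool from a paired t-test, with effect size 0.86, significance level 0.05 and 90% power.

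No two-sample test is named anywhere in the article.

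**The concern.** A paired t-test and a signed rank test both work on one difference per subject, so each child must supply both an exoskeleton change and a standard-therapy change. The first-period restriction removes one of the two from every child. What remains is one change per child in two separately randomised groups.

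The primary endpoint is a before-and-after change with no concurrent control, in children who are growing and receiving therapy. The Abstract and the Hypotheses section both claim greater improvement than under standard therapy, and this comparison is the only named analysis of that claim. An analyst following the text would have to do one of three things: match unrelated children arbitrarily, bring back second-period data that the plan excludes, or choose a different test at the time of analysis. The plan should settle this before data are seen.

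**Working it through.** **Step 1. What the first period contains**

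| | First-period treatment | Change available | Other treatment's change |
|---|---|---|---|
| Group A | Exoskeleton | Initial to Final | None in this period |
| Group B | Standard therapy | Baseline to Standard | None in this period |

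The order of assessments is given in Study assessments and outcomes. No child has an entry in both change columns, so the number of pairs is zero. This settles the point without any calculation.

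**Step 2. The article's own sample size**

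Inputs from Statistical considerations: d = 0.86, alpha = 0.05, power 90%, paired t-test. Power comes from the noncentral t distribution with n − 1 df and noncentrality d × √n.

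- n = 13: noncentrality = 0.86 × √13 = 3.10. One-sided power is 0.899 and two-sided power 0.812.
- Recruitment: 13 / (0.80 × 0.75) = 21.7, so 22 per pool.

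The stated 13 is reproduced as a one-sided paired calculation, and the 22 is reproduced as well. The article does not state sidedness, and that is a separate matter. What matters here is that the 13 fits the within-child Initial-to-Final test, not a comparison of two groups.

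**Step 3. The comparison that the restriction implies (illustration)**

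Assumptions: true difference in change of 10 degrees; SD of change of 12 degrees in each group (the article's 3 degrees × its safety factor of 4); two-sided 0.05. The article gives no SD for change under standard therapy and no first-period group sizes.

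Standard error = 12 × √(1/n₁ + 1/n₂). Half-width of the 95% CI = t(0.975, n₁ + n₂ − 2) × standard error. Noncentrality = 10 / standard error.

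| Split (assumed) | df | Standard error | Half-width, degrees | Power |
|---|---|---|---|---|
| 7 v 6 (13 per pool) | 11 | 6.68 | 2.201 × 6.68 = 14.7 | 28% |
| 7 v 9 | 14 | 6.05 | 2.145 × 6.05 = 13.0 | 34% |
| 7 v 11 | 16 | 5.80 | 2.120 × 5.80 = 12.3 | 37% |
| 11 v 11 (all 22) | 20 | 5.12 | 2.086 × 5.12 = 10.7 | 46% |

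The middle rows allow for Group B children supplying standard-therapy data before any opt-out from community use. With 11 randomised per group, 11 × 0.80 × 0.75 = 6.6, about 7, remain for exoskeleton data. Group B has between 11 × 0.80 = 8.8, about 9, and all 11.

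**Step 4. Forcing pairs**

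Matching 6 children from each group at random gives 5 df and a half-width of 2.571 × 12 × √(2/6) = 17.8 degrees, with power of about 22%. The 7 v 6 two-sample analysis gives 14.7 degrees and 28%.

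**The case against.** Several points on the other side have force.

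- **The comparison is secondary.** The article labels it so, and the primary within-child test is properly paired. A reader might infer that the primary analysis is invalid. The documents do not support that, because each child has both an Initial and a Final value.
- **The own-control phrase.** The Discussion justifies the crossover design as "while also allowing each to serve as their own control". A reader might take this as a direct contradiction of the first-period comparison. It is a general design rationale and remains true of the primary test. The Discussion also says that differences both within and between participants will be evaluated, so a between-child comparison was foreseen. At most, the phrase needs a clarification that it does not describe this contrast.
- **The numerical harm is modest.** Pairing made without sight of the outcomes loses precision and has no unique answer, but it would not inflate the type I error. The fall from 28% to 22% is small. The low power comes mainly from the number of children, not from the choice of test.
- **The group sizes and SD are assumed.** This is so, and the powers in the working are illustrations only.
- **A statistical analysis plan may correct it.** That would excuse silence. Here the article names a specific test that does not fit the data it specifies.

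None of these supplies the missing pairs. Reading the sentence as two separate within-group tests does not help either, because the text compares one change with the other and separate tests do not estimate that difference.

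**Conclusion.** The point stands as a specification error in a secondary but important comparison. With first-period data only, no pairs are defined, so neither the paired t-test nor the signed rank fallback can be run as written. The same holds for the secondary outcomes compared with standard therapy. This conclusion rests on the article's text alone.

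The sample size of 13 per pool does not give 90% power for this contrast. Under the stated assumptions (SD 12 degrees, difference 10 degrees, two-sided 0.05), power runs from about 28% with 7 v 6 to about 46% with 11 v 11.

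**What to change.** 1. Within each diagnosis pool, replace the paired test for this contrast with an independent-groups comparison of the first-period changes as the protocol defines them: Initial to Final in Group A, Baseline to Standard in Group B. Use a two-sample t-test or a linear model of change on group, optionally adjusted for the pre-randomisation Baseline value. Name the rank-sum test as the fallback.
2. Make the same replacement for the secondary outcomes compared with standard therapy.
3. If an end-of-period value adjusted for Baseline is preferred, say that it is a different contrast. In Group A it would also take in the 12-week set-up and accommodation block, so about 24 weeks would be set against 12 weeks in Group B.
4. State that 13 per pool was sized for a paired test and does not give 90% power here. Present the comparison with its confidence interval accordingly.
5. Clarify in the Discussion that the own-control rationale does not describe the first-period comparison.

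The cost is a wording change to the protocol and any analysis plan. No new data or visits are needed.

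### Re-sizing the trial from the observed interim effect in about 6-7 children per pool, then running an ordinary paired t-test, does not guarantee the 5% level and gives an imprecise new sample size

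*Protocol article*

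**What the plan says.** All of this is in the protocol article, Statistical considerations, unless noted.

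- Size: "At a significance level of 0.05 and 90% power we estimate that 13 participants within each subject pool is required". The calculation is for a paired t-test. The inputs are a "targeted mean improvement in peak knee extension during midstance, which was approximated as 10.0 degrees", and an "observed standard deviation of ± 3 degrees (n = 3) and a safety factor of 4"; the standardised effect is given as 0.86.
- Recruitment: "We estimated about 80% of enrolled participants would complete the study through the final outcome assessment". A further 25% are expected to finish but opt out of community use. This leads to 22 recruited per pool, "setting the maximum number of participants as 44".
- Interim: at 50% of the estimated recruitment number the primary endpoint is analysed "to evaluate the effect and the power and revise the total enrollment number if indicated".
- Final analysis: a per-protocol paired t-test between the initial and final assessments, reported with a 95% confidence interval.
- Study population: the cerebral palsy pool and the pool of other neuromuscular disorders are analysed separately.

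**The concern.** The stated input to the re-sizing is the effect itself, not only the variability or the retention rate. When N depends on the interim effect, the stage-one data enter the final statistic with a weight that depends on their own value. A promising stage one can be locked in by stopping small, and a weak one can be diluted by adding children. The ordinary t-test ignores this, so its p-value and confidence interval need not have their nominal error rates.

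The second issue is precision. An effect estimated in six or seven children says little about how many are needed. Such a rule could shrink a sound trial below its planned size or enlarge it severalfold, in a paediatric study already planned to last six years.

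**Working it through.** **Step 1: the plan's own figures.** SD 3 x 4 = 12 degrees and 10/12 = 0.833, close to the stated 0.86. Exact paired t-test power (noncentral t, n - 1 degrees of freedom) at d = 0.86 and n = 13 is 89.9% one-sided and 81.2% two-sided. The stated 13 is thus recovered, within rounding, as a one-sided 5% test; a two-sided test needs 17. The article does not state sidedness, so both were tried below. For recruitment, 0.80 x 0.75 = 0.60 and 13/0.60 = 21.7, so 22 per pool. This reproduces.

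**Step 2: children available at the interim.** Half of 22 is 11 per pool, and 11 x 0.60 = 6.6; half of 13 is 6.5. So about 6-7 are evaluable, or 11 with no losses. If the look is taken the moment the 11th child is recruited, fewer will have a final assessment.

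**Step 3: type I error.** Simulation under no effect (200,000 trials per setting, two-sided 5%):
- draw n1 changes and compute the observed d = mean/SD;
- set N to the smallest n with 90% power at that d, within the cap;
- add the remaining children and run an unadjusted t-test on all of them.

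The caps are assumptions. A cap of 22 evaluable per pool corresponds to 22 recruited with no losses. At 60% yield, 22 and 26 evaluable need 22/0.60 = 37 and 26/0.60 = 44 recruits per pool.

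| Interim n | Cap (evaluable) | N may only rise from 13 | N may rise or fall |
|---|---|---|---|
| 6 | 26 | 5.9% | 7.0% |
| 6 | 44 | 6.3% | 7.5% |
| 7 | 26 | 5.9% | 6.7% |
| 11 | 22 | - | 5.7% |
| 11 | 26 | - | 5.8% |

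With a cap of 22 and 6-7 at interim, the rise-only figure is 5.7%. Over caps of 22-44 with 6-7 children, the ranges are about 5.7-6.4% (rise only) and 6.5-7.6% (either way). One-sided testing over the same caps gives 5.5-6.2% and 6.2-7.1%.

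Other rules behave differently:
- N held within 13, reductions only: 5.9-6.2%.
- Increase only, returning to 13 if the cap (22 or 26) is exceeded: 4.6-4.9%.
- Binding futility stop when N exceeds the cap: 2.0-4.4%.

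**Step 4: stability of the new N.** True d equal to the planning value 0.86, two-sided, 90% power, no cap:

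| Interim n | Median N | Middle 50% | Middle 80% | N of 13 or fewer | N above 22 |
|---|---|---|---|---|---|
| 6 | 15 | 9 to 33 | 6 to 93 | 45% | 36% |
| 7 | 16 | 9 to 31 | 6 to 78 | 43% | 35% |
| 11 | 16 | 10 to 27 | 8 to 51 | 40% | 33% |

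At d = 0.833 with 6-7 children the quartiles are about 9 to 35. If the observed d is 0.86, its 95% interval is -0.12 to 1.78 with 6 children and -0.04 to 1.72 with 7.

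**Step 5: does re-sizing on the SD alone cure it?** Not fully. SD-only, upward-only re-sizing with a naive final t-test still gives about 5.5%. A fixed-weight inverse-normal combination (weights 6/13 and 7/13) gives 5.0%. The SD is also imprecise: its 95% interval runs from 0.62 to 2.45 times the estimate with 6 children, and from 0.64 to 2.20 with 7.

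**The case against.** The article is a condensed account, and an analysis plan that is not shown may hold the re-sizing rule, the cap and an adjusted final test. The text does not say that N may fall, and the 0.05 stands in the sample-size sentence rather than beside the final test. The study describes itself as analogous to phase I/II, and the excess in most scenarios is one to two points. The number at interim is derived, and the look might be taken at 22 of 44 overall with unequal pools. All of this stands, and it limits the point. It does not remove it, because the article itself makes the observed effect an input to enrolment, and no later adjustment of the final test makes an effect from 6-7 children informative about N.

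Four stronger readings are tempting but not supported:
- That the 5% level is certainly exceeded, by a known amount. The size depends on a rule the article does not give, and some rules hold 5%.
- That success may be claimed at the interim, which would inflate the error further. The only stated use is to revise enrolment.
- That the new N would be little more than noise. The wide spread in Step 4 is for an uncapped rule. With increases only and a cap of 26, the quartiles are 13 to 26 (median 16).
- That revising enrolment contradicts the maximum of 44. That number follows from the current assumptions, and the same section openly allows total enrolment to be revised. It needs restating, but it is not an inconsistency.

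**Conclusion.** The point holds in limited form. Effect-driven re-sizing followed by an ordinary paired t-test does not guarantee 5%. With 6-7 evaluable children per pool and N re-set for 90% power at the observed effect, the error is roughly 5.7-6.4% if N may only rise and 6.5-7.6% if it may also fall. With 11 children and caps of 22-26, the either-way figure is 5.7-5.8%. These values assume normal changes, caps of 22-44 evaluable per pool, no early success claim and no adjustment held elsewhere.

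The imprecision of the re-estimated N is the firmer part, because it does not depend on how the final test is done. This should be fixed before the interim data are seen. Given the early-phase purpose and the modest, rule-dependent inflation, it does not by itself invalidate the trial.

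**What to change.** Do not re-size on the observed effect. There are two acceptable routes.

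1. **Feasibility only (simpler).** Limit the interim to evaluable yield and compliance, and remove the evaluation of effect and power. The final paired t-test then stands as planned. The cost is a wording change and giving up the chance to correct a wrong SD.

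2. **Re-size on nuisance quantities.** Recompute N from the SD of change and the evaluable yield, keeping the 10-degree target fixed. Allow increases only, with a floor of 13 evaluable per pool and a stated cap that replaces or confirms 44. Analyse each pool with Z = sqrt(6/13) x z1 + sqrt(7/13) x z2, where z1 and z2 are the normal scores of the one-sided p-values from the children of each stage alone. Fix the weights in advance and derive the confidence interval from the same combination. The cost is a slightly more complex final analysis and a small efficiency loss from the fixed weights.

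Because the SD from 6-7 children is itself imprecise, route 1 is preferable unless there is a strong reason to keep re-sizing. Under either route, state whether the look is per pool or overall, and whether the 50% counts children recruited or children with a final assessment.
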